### Cost-effectiveness study

The economic evaluation will be performed from a healthcare perspective, for a period of one year post-inclusion per patient. Data on total in-hospital medical care will be obtained from medical files, using a standardized and piloted data extraction form. Medical costs will be calculated by multiplying the volumes of healthcare use with the corresponding unit prices. Unit prices will be calculated for all six countries separately. Costs for inpatient days in hospital will be estimated as real, basic costs per day using detailed administrative information. For other cost prices we will use charges. The unit price of the ACP intervention will be determined with the micro-costing method, which is based on a detailed assessment of all resources used. To compare the relative costs and outcomes of ACP versus ‘care as usual’ we will calculate the Incremental Cost Effectiveness Ratio (ICER); the average additional costs of ACP divided by the average change in emotional functioning measured with the EORTC-QLQ-C30 emotional functioning subscale (4 items). A sensitivity analysis will be performed to assess the stability of the results to changes in costs and effectiveness parameters (EORTC QLQ-C15-PAL quality of life subscale), and differences in healthcare systems between the European countries.

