Questionnaire study. Patients will be asked to complete a written questionnaire about quality of life, symptoms, the decision-making process, patient activation, coping, and satisfaction with care (and the intervention) at baseline (i.e., the moment of inclusion, before the ACP program is delivered in the intervention group), and at 2.5 and 4.5 months after inclusion. If a patient dies during follow up (i.e., within one year after inclusion), a relative identified by the patient as next of kin will receive a questionnaire to assess the patient’s quality of end-of-life care and the relative’s own wellbeing.Medical file study. Data on patients’ survival will be collected, as well as preferences as documented and care as received to assess whether patients’ preferred care was congruent with received care. Data on care as received will also be used in the cost-effectiveness analysis. These medical files will be studied one year post-inclusion with a checklist.Study of recorded ACP sessions. Data will be obtained from audio recorded facilitated interview sessions. Compliance with the intervention will be systematically evaluated with a predefined checklist.

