In ACTION, we expect to encounter some challenges and possible limitations. First, patients may decline participation for different reasons. They may feel overwhelmed by the topics raised in the ACP intervention sessions and may not (yet) feel prepared to talk about these issues. We will use a patient-centered approach to facilitate study participation. Patients will receive information about the project through their treating specialist. Since patients may refuse because they do not want to engage in ACP conversations, non-response bias cannot be ruled out. Also selection bias cannot be ruled out, e.g. in intervention hospitals’ where including physicians may be more likely to ask patients who they think are more ‘open’ to ACP to participate in the study. If such ‘gatekeeping’ comes into play, the effect of the intervention may be overestimated. However, our approach to systematically assess all lung and colorectal cancer patients for eligibility, and subsequently invite all who are eligible to participate in the study may reduce this risk. Attrition is another potential limitation to this project. Attrition may occur because the condition of the patient might worsen such that further participation becomes impossible, or patients might die during follow-up. We try to limit attrition by adding the inclusion criterion of a minimal anticipated life-expectancy of three months and to measure our main outcome measure at 2.5 months. Third, the international character of this project might be a challenge, as a balance needs to be found between on the one hand testing a uniform intervention in the six countries, that on the other hand is tailored to the specific cultural, ethical and legal context of each country. Fourth, the extent to which actual care will be reflected in medical files can be questioned. Potentially, not all treatments that patients receive will be documented in the hospital medical files.

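### The one-year 'healthcare perspective' ICER costs only in-hospital care plus the intervention, and at least 7.5 of its 12 cost months have no matching outcome

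*Protocol article*

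**What the plan says.** The section on the cost-effectiveness study sets perspective and horizon: "The economic evaluation will be performed from a healthcare perspective, for a period of one year post-inclusion per patient". It then names the source of resource use: "Data on total in-hospital medical care will be obtained from medical files, using a standardized and piloted data extraction form". The only other cost component described is the programme itself: "The unit price of the ACP intervention will be determined with the micro-costing method, which is based on a detailed assessment of all resources used". The ratio is defined as "the average additional costs of ACP divided by the average change in emotional functioning measured with the EORTC-QLQ-C30 emotional functioning subscale (4 items"), with no time point for the effect. A sensitivity analysis is planned on costs, on an alternative quality-of-life subscale and on differences between healthcare systems.

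Under Measurements, patients complete the questionnaire at baseline "and at 2.5 and 4.5 months after inclusion". The medical files are reviewed one year after inclusion, and that file study feeds the cost-effectiveness analysis. Table 2 lists specialist palliative care input among the items taken from those files. The Discussion concedes that, potentially, "not all treatments that patients receive will be documented in the hospital medical files", but draws no consequence for the economic evaluation.

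**The concern.** Two features of the ratio do not fit its description.

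First, a healthcare perspective covers care wherever it is delivered within the healthcare system, whereas the data described cover the hospital. In this trial the gap is unlikely to be neutral between arms. The Background credits ACP with the potential to reduce unneeded hospital admissions and treats wishes about place of residence at the end of life as central. The Intervention section gives declining hospitalisation as an example of a preference to be recorded. A patient cared for at home or in a hospice instead of on a ward would show lower hospital cost, and whatever replaced the ward would not appear.

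Second, costs accumulate over 12 months, while the effect is a score observed no later than 4.5 months. The ratio would read as one year's cost per point of emotional functioning, yet nothing is known about emotional functioning for most of that year.

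Cost-effectiveness is a named secondary endpoint and objective, and the Dissemination section describes an Advisory Board of future policy users. Such a reader would take a one-year healthcare-perspective ICER at face value.

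**Working it through.** **The plan's own figures.** The article states no cost or ICER, so there is none to reproduce. The attrition figures that govern who supplies the effect do reproduce: 15% deaths + 10% other dropout = 25% by 2.5 months; 34 × 0.75 = 25.5 per hospital and tumour type, stated as 25.

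**1. Scope of the costs.** Set against the stated perspective:

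| Component | Source described? |
|---|---|
| In-hospital care, 12 months | Yes, medical files |
| ACP intervention | Yes, micro-costing |
| Specialist palliative care input | Yes, as far as it appears in medical files (Table 2) |
| General practice, home nursing, nursing home, hospice | None |

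**2. What uncosted substitution could do.** Let H be the hospital cost averted per patient, c the intervention cost, and f the cost of replacement care as a share of H. None of these is in the documents; all values below are assumptions.

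- True saving on care = H(1 − f); recorded saving = H. Overstatement = 1/(1 − f): 1.33 at f = 0.25 and 2 at f = 0.50.
- Recorded cost increment = c − H; healthcare-perspective increment = c − H + fH.

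With c = 300:

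| H | Recorded | f = 0.25 | f = 0.50 | f = 0.75 | f = 1 |
|---|---|---|---|---|---|
| 500 | −200 | −75 | +50 | +175 | +300 |
| 1000 | −700 | −450 | −200 | +50 | +300 |
| 2000 | −1700 | −1200 | −700 | −200 | +300 |

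The increment changes sign at f = 1 − c/H: 40% for H = 500, 70% for H = 1000 and 85% for H = 2000. At f = 0 the two perspectives agree. The table shows that the conclusion could turn on the missing component. It does not show that it will.

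**3. Time windows.** Cost window: 12 months. Last emotional-functioning measurement: 4.5 months.

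- Cost months after the last measurement: 12 − 4.5 = 7.5, and 7.5/12 = 62.5%.
- If the effect is taken at the primary time point: 12 − 2.5 = 9.5, and 9.5/12 = 79%.

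**4. How much happens in the unmatched months.** The share dying within the cost year depends on how the article's survival statements are read. Under a constant hazard (assumption):

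- 15% dead at 2.5 months: survival at 12 months = 0.85^(12/2.5) = 0.46, so about 54% die.
- Life expectancy of about one year read as a mean: 1 − exp(−1) = 63% die. This reading implies 19% dead at 2.5 months, more than the 15% that the article calls conservative.
- Read as a median: 50% die.

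So roughly 50% to 63% die within the cost year. Their hospital costs near death are counted, and for those who die after 4.5 months these costs fall after the last outcome measurement. Hospital files can in principle supply costs for all 1,360 patients; at 25% attrition, about 1,360 × 0.75 = 1,020 supply a score at 2.5 months.

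**The case against.** The strongest reply is that this is a secondary analysis in a condensed article that already discloses incomplete hospital files, includes the intervention cost (which counts against ACP), collects specialist palliative care input, and plans sensitivity analyses on costs and healthcare systems. Part of this stands. The costs are not hospital costs alone, and the primary result is untouched. But a disclosed gap in the files is not a source of out-of-hospital data, and the sensitivity analyses as described add none. The article names both its perspective and its data source, and the two do not match. That is a stated inconsistency, not a detail left to a fuller plan.

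Four stronger readings are tempting and are not supported.

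- A reader might infer that the ICER is biased towards ACP. That holds only if hospital care is replaced by uncosted care elsewhere. The documents make this plausible but do not quantify it, and the mismatch in windows by itself has no direction.
- A reader might take the denominator, "the average additional costs of ACP divided by the average change in emotional functioning", as a within-arm change whose sign could be wrong in a deteriorating population. The sentence opens by comparing ACP with usual care and names an incremental ratio, so a between-arm difference is the natural reading. Only the time point needs stating.
- A reader might conclude that the effect will be computed in survivors only. The article does not say how deaths and missing scores enter, and the full plan may. No plan, however, can supply scores after 4.5 months that are not collected.
- A reader might want the one-year ICER replaced by a 2.5-month ICER in the same responding patients. That would discard most end-of-life hospital costs, which ACP is expected to affect, and drop about a quarter of patients, contrary to the intention-to-treat principle stated under Analyses.

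**Conclusion.** The point holds in two parts. The stated healthcare perspective is broader than the costs described, which are in-hospital care plus the intervention. If ACP shifts care out of hospital, savings could be overstated by an amount the documents cannot quantify; the multipliers and sign changes above rest wholly on assumed values. In addition, at least 7.5 of the 12 cost months (62.5%), or 9.5 (79%) if the effect is taken at 2.5 months, have no matching outcome. That follows from the stated schedule without any assumption, and its effect on the ICER could go either way. The change should be made because it alters what the trial may claim about cost-effectiveness; it does not bear on the primary endpoint.

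**What to change.** In the methods and in any conclusion, restate the perspective as a hospital perspective (in-hospital care plus intervention cost), and limit cost-effectiveness claims to that. State that the effect term is the between-arm difference in emotional functioning at 2.5 months, the primary time point. Keep the one-year cost comparison in all included patients by intention to treat. Add, as a sensitivity analysis, an ICER in which file-derived costs are cut at the date that closes the effect window, so that the reader can see how far the result depends on costs with no matching outcome.

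The cost is a narrower claim, resource use that can be dated in the file extraction, and one further analysis. No new data collection from patients is needed. Keeping the healthcare-perspective label would instead require out-of-hospital use to be collected.

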### Dissemination

We have set up an Advisory Board of future international policy users of the project results. The role of the Advisory Board will be to provide a critical perspective throughout the life of the project. The project results will be disseminated through publications in scientific journals and conferences. To disseminate the knowledge to all stakeholders we will use the project website (www.action-acp.eu). A link of ACTION to the websites of the consortium and Advisory Board members will be featured.

## Discussion

This project aims to study the effects of the Respecting Choices program on quality of life and symptoms of patients with advanced lung or colorectal cancer. This study has several strengths. First, studies about Advance Care Planning have mainly been performed with older nursing home patients. Transferring the concept of ACP from care of the elderly to patients with advanced cancer, who on average are younger and remain competent for a larger part of their disease trajectory, is a highly relevant next step in an era of increasing focus on patient centered healthcare and shared decision-making. Second, a randomised controlled trial design will enable us to draw conclusions about the causal relations between ACP and the outcomes under study. The clustered design of this project prevents contamination between the control and intervention group. Third, the unique combination of quantitative and qualitative methods in this project will result in profound insights into the underlying working mechanisms of ACP.

In ACTION, we expect to encounter some challenges and possible limitations. First, patients may decline participation for different reasons. They may feel overwhelmed by the topics raised in the ACP intervention sessions and may not (yet) feel prepared to talk about these issues. We will use a patient-centered approach to facilitate study participation. Patients will receive information about the project through their treating specialist. Since patients may refuse because they do not want to engage in ACP conversations, non-response bias cannot be ruled out. Also selection bias cannot be ruled out, e.g. in intervention hospitals’ where including physicians may be more likely to ask patients who they think are more ‘open’ to ACP to participate in the study. If such ‘gatekeeping’ comes into play, the effect of the intervention may be overestimated. However, our approach to systematically assess all lung and colorectal cancer patients for eligibility, and subsequently invite all who are eligible to participate in the study may reduce this risk. Attrition is another potential limitation to this project. Attrition may occur because the condition of the patient might worsen such that further participation becomes impossible, or patients might die during follow-up. We try to limit attrition by adding the inclusion criterion of a minimal anticipated life-expectancy of three months and to measure our main outcome measure at 2.5 months. Third, the international character of this project might be a challenge, as a balance needs to be found between on the one hand testing a uniform intervention in the six countries, that on the other hand is tailored to the specific cultural, ethical and legal context of each country. Fourth, the extent to which actual care will be reflected in medical files can be questioned. Potentially, not all treatments that patients receive will be documented in the hospital medical files.

## Conclusion

Advanced cancer typically involves multiple symptoms and seriously affects patients’ quality of life. Focusing care at patients’ preferences and open and respectful communication are important values in end-of-life care, yet these have been found to be a challenge for healthcare professionals as well as for patients and relatives. Little is known about the outcomes of formal ACP, the effects of formal ACP on medical care and medical decision-making, costs and cost-effectiveness of formal ACP and country-specific factors that might influence ACP. Our project will fill these gaps in knowledge, based on an international multicenter cluster-randomised clinical trial to test the outcomes and effects of a formal ACP program, which is enriched by a qualitative study and a cost-effectiveness study.

Contact: www.action-acp.eu

## Abbreviations

ACP: Advance Care Planning
ACTION: Advance Care Planning; an Innovative Palliative Care Intervention to Improve Quality of Life in Cancer patients – a Multi-Centre Cluster Randomised Clinical Trial
DSMB: Data Steering Monitoring Board
EORTC: European Organisation for Research and Treatment of Cancer
ICC: Intra-Class Correlation
ICER: Incremental Cost Effectiveness Ratio
QLQ: Quality of Life Questionnaire
